The randomization sequence was generated by an independent statistician using simple randomization. The sequence was then integrated into the backend of the customized WeChat mini-program. After a participant completed the baseline survey and was confirmed eligible, the system automatically executed the group assignment. Allocation concealment was strictly implemented. After a participant completed the baseline assessment and was confirmed eligible, the system automatically executed the group assignment based on the preloaded, concealed sequence. Until this point of allocation, neither the participant, the research coordinator enrolling the participant, nor the outcome assessors could access or predict the upcoming assignment. The allocation is only revealed to the system and the intervention coordinator after the participant’s baseline data is irrevocably locked and enrollment is finalized. The participants are blinded to group assignment. Outcome assessors and data analysts remain blinded to group assignment throughout the trial. They have access only to deidentified participant data coded with unique study IDs, without any information linking the ID to the intervention arm.

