#### Brief PrEP Motivational Interviewing

The brief motivational interviewing sessions are conducted by experienced professionals with demonstrated expertise in both PrEP provision and motivational interviewing techniques. These 1-on-1 sessions (delivered face-to-face or online) are tailored to each participant’s specific stage within the PrEP motivational cascade, such as objective identification, PrEP precontemplation, PrEP contemplation, PrEP preparation, PrEP action and initiation, and PrEP maintenance. Content is individualized to address specific barriers currently present, informed primarily by findings from the participant’s most recent assessment phase. This targeted approach aims to resolve impediments to PrEP engagement through structured, theory-guided dialogue.

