#### Conditional Economic Incentives

Participants in the combined intervention arm also receive additional peer GCEIs on top of the HAPA intervention. Incentive information is communicated immediately at the start of the intervention. The incentive amounts are determined at the end of the 3-month intervention by the researchers based on the overall completion status of each participant and their peer group according to predetermined conditions.

Participants are formed into peer groups of approximately 6 individuals. These groups participate in structured in-person sessions. Activities are designed to include: introductions and icebreakers, PrEP knowledge quizzes, partner dialogues, “Voicing My Barriers” roundtable discussions, and PrEP scenario role-playing. The objectives are to foster trust, enable deeper peer connection, enhance group belonging, strengthen HIV prevention awareness, identify and overcome barriers to PrEP use, and ultimately increase PrEP initiation rates. Six participants form a peer group, and the economic incentive amount is based on the average completion level of the group. Group-level economic incentives are stepwise reduced based on the group’s average PrEP initiation rate. Participants qualify for US $22 if their group achieves an 80%‐100% rate, US $11 for a 50%‐79% rate, and US $0 for rates below 50%. PrEP initiation is operationally defined as the documented provision of a physician-issued prescription.

The WeChat mini-program automatically records intervention process evaluation indicators, including: (1) whether each participant has read the information messages; (2) the reading time for each message; and (3) each participant’s judgment of whether the information was helpful.

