### Intervention Delivery and Follow-Up Status

Following the baseline assessment, the 3-month active intervention period commenced in January 2026. The intervention delivery, including tailored WeChat messaging, scheduled motivational interviews, and structured in-person group sessions for the HAPA+GCEI arm, is scheduled for completion in April 2026.

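### The protocol says participants are blinded to their arm, but its own description of the arms rules this out, so the participant-reported secondary outcomes are unblinded

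*Protocol article*

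**What the plan says.** The blinding text is in the Methods, under Study Population and Participant Recruitment, in the paragraph on randomization. It first describes concealment up to the moment of allocation. It then says who learns the result afterwards: "The allocation is only revealed to the system and the intervention coordinator". The next sentence reads: "The participants are blinded to group assignment". A separate claim follows: "Outcome assessors and data analysts remain blinded to group assignment throughout the trial".

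The Intervention and Control sections describe what each arm receives.

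- **Combined arm.** "Participants in the combined intervention arm also receive additional peer GCEIs on top of the HAPA intervention". On timing: "Incentive information is communicated immediately at the start of the intervention". Participants are put in peer groups of about six, and "These groups participate in structured in-person sessions". The payment is US $22, US $11 or US $0, depending on the group's initiation rate.
- **Both HAPA arms.** Tailored messages three times a week, plus motivational interviews: "These 1-on-1 sessions (delivered face-to-face or online) are tailored to each participant".
- **Control.** Non-personalized prevention messages twice a week.

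Under Outcomes, the primary outcome is PrEP initiation based on a doctor's prescription. The secondary outcomes are adherence, intention to pay, PrEP stigma, and changes in condom use and in number of partners.

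**The concern.** Participant blinding means that a participant cannot tell which arm he is in. Here the arms differ in things that a participant sees and does: being promised money, attending group meetings, having an individual interview, or having none of these. An incentive cannot work on someone who does not know about it.

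What is at stake is how the secondary results are read. Someone who takes the sentence at face value would treat the self-reported outcomes as protected from expectation and social desirability. They are not, and the limitations in the Discussion do not mention it. The Discussion also presents adherence as objectively measured, whereas Outcomes bases it on self-report and a calendar kept in the mini-program.

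**Working it through.** No figure in the plan depends on this sentence, so the check is one of consistency between sections.

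**1. Can the sentence refer only to the time before allocation?** No. Concealment before allocation is described separately and earlier in the same paragraph. The blinding sentence comes after the text on what happens once baseline data are locked, and it stands next to a claim about assessors and analysts that covers the whole trial.

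**2. Is it compatible with each arm as delivered?**

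| Feature visible to the participant | HAPA (n=128) | HAPA + incentive (n=126) | Control (n=127) |
|---|---|---|---|
| Messages | tailored, 3 per week | tailored, 3 per week | generic, 2 per week |
| One-on-one interview | yes | yes | none described |
| In-person peer group | none described | yes | none described |
| Announced payment by group result | none described | yes, up to US $22 | none described |

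The Results section (Intervention Delivery and Follow-Up Status) confirms which arm attends the group meetings: "structured in-person group sessions for the HAPA+GCEI arm".

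- For the combined arm, 126 of 381 participants (126/381 = 33%), the contradiction is complete: the participant is told of a feature that only this arm has.
- Taking both HAPA arms together, 128 + 126 = 254 of 381 (67%) receive an interview for which control has no counterpart.
- No sham interview, attention-matched contact or dummy payment is described for control.

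**3. Could disclosure have been limited so that participants do not recognise their arm?** The article does not say so. Measurements and Follow-Ups says participants are told the aims, content and procedures of the study, and Ethical Considerations says they are fully informed of objectives and procedures. Neither describes withholding the other arms' content or the hypotheses.

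**4. Which outcomes does this touch?**

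| Outcome | Source | Exposure to reporting bias |
|---|---|---|
| PrEP initiation (primary) | documented physician's prescription | much lower; not a participant's rating |
| Adherence | self-report and self-kept calendar | open |
| Intention to pay | questionnaire | open |
| PrEP stigma | questionnaire scale | open |
| Condom use | questionnaire | open |
| Number of partners | questionnaire | open |

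All five listed secondary outcomes depend on participant report, and the primary outcome does not. The documents contain nothing from which the size of the bias could be computed.

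**The case against.** The strongest defence has three parts.

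**Knowing what one receives is not knowing one's arm.** HAPA-only and control participants both get WeChat messages, and the article says allocation is disclosed only to the system and the coordinator. A control participant might not know what the others receive. The consent pages are not available, so what each participant was told about the other arms cannot be checked. This stands in part: the contradiction is plainest for the combined arm and less absolute between HAPA alone and control. It does not rescue an unqualified sentence about all participants. It does mean that stating exactly what is withheld is as valid a correction as deleting the claim.

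**The main result is largely unaffected.** The primary outcome is a documented prescription, and responding to a known incentive is part of the effect under test. This stands. No sample size, model or primary comparison changes.

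**It is too late to blind anyone.** Randomization is complete and the intervention began in January 2026. That is true, but the point concerns what the protocol claims and how the results are read, and both can still be corrected.

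A reader might go further and infer three things that the documents do not support.

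- *That analyst and assessor blinding also fails*, because peer-group membership, incentive tier and interview records exist only in some arms. The article says these staff hold only de-identified data with nothing linking the ID to the arm. Nothing places those records in their dataset, and separate staff or coded labels could preserve the blinding.
- *That incentive calculation and outcome verification are done by the same people.* The article says only that the researchers set the incentives. It does not say that they are the assessors.
- *That the bias favours the intervention on every secondary outcome.* The intervention promotes PrEP use, but condom use and partner number are followed as possible risk compensation, and condom information is described for control. Pressure on those answers could run either way.

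**Conclusion.** The concern holds in a limited form. The statement that participants are blinded is wrong as written, because the article's own description of the arms and of disclosure excludes it. The error is one of a stated design property, not of an omitted detail, so neither the condensed article format nor an unseen analysis plan explains it.

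The consequence is confined to the five secondary outcomes that rest on participant report. They are open to expectation and desirability bias whose size and direction the documents do not allow one to state. The claim about assessors and analysts is not contradicted.

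The conclusion assumes that the arms are delivered as described and that nothing unreported in the consent process hides the arms from participants. If something is hidden, the sentence still needs to say what. This is a correction worth making before results are reported, but it is not a threat to the primary comparison.

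**What to change.** 1. In Study Population and Participant Recruitment, replace the participant-blinding sentence with a statement that participants are not blinded to their arm. If something is withheld, such as the content of the other arms or the hypotheses, say exactly what and from whom.
2. Keep the statement on outcome assessors and data analysts.
3. Under Outcomes, mark adherence, intention to pay, stigma, condom use and number of partners as participant-reported and unblinded.
4. Add to the limitations that these outcomes may carry expectation and desirability bias of unknown size and direction, and interpret between-arm differences in them accordingly. Say there that the prescription-based primary outcome is much less exposed to reporting bias.

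The cost is a few sentences, with no new participants, data or analyses. Final follow-up is scheduled for August 2026 and database lock for December 2026, so the change can be made before analysis. The only downside is that the stated design looks slightly less favourable.

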### Intervention

#### Tailored Health Messages

Participants receive a 3-month mobile health intervention guided by the HAPA. Tailored messages are developed using behavior change techniques based on theoretical guidance [34]. Three times weekly, the personalized health message is randomly delivered to participants via the WeChat mini-program. These messages are drawn from an information library designed based on HAPA theory, expert input, and literature review, and are tailored to the participant’s current PrEP using status. For example: participants exhibiting low risk perception receive messages incorporating vivid illustrations of potential health risks associated with their PrEP adherence status, using real-life case studies and epidemiological data to enhance awareness. Participants with low self-efficacy receive messages incorporating techniques such as providing success stories of similar individuals overcoming adherence challenges and offering step-by-step guidance to bolster confidence in maintaining the PrEP regimen.

#### Brief PrEP Motivational Interviewing

The brief motivational interviewing sessions are conducted by experienced professionals with demonstrated expertise in both PrEP provision and motivational interviewing techniques. These 1-on-1 sessions (delivered face-to-face or online) are tailored to each participant’s specific stage within the PrEP motivational cascade, such as objective identification, PrEP precontemplation, PrEP contemplation, PrEP preparation, PrEP action and initiation, and PrEP maintenance. Content is individualized to address specific barriers currently present, informed primarily by findings from the participant’s most recent assessment phase. This targeted approach aims to resolve impediments to PrEP engagement through structured, theory-guided dialogue.

#### Conditional Economic Incentives

Participants in the combined intervention arm also receive additional peer GCEIs on top of the HAPA intervention. Incentive information is communicated immediately at the start of the intervention. The incentive amounts are determined at the end of the 3-month intervention by the researchers based on the overall completion status of each participant and their peer group according to predetermined conditions.

Participants are formed into peer groups of approximately 6 individuals. These groups participate in structured in-person sessions. Activities are designed to include: introductions and icebreakers, PrEP knowledge quizzes, partner dialogues, “Voicing My Barriers” roundtable discussions, and PrEP scenario role-playing. The objectives are to foster trust, enable deeper peer connection, enhance group belonging, strengthen HIV prevention awareness, identify and overcome barriers to PrEP use, and ultimately increase PrEP initiation rates. Six participants form a peer group, and the economic incentive amount is based on the average completion level of the group. Group-level economic incentives are stepwise reduced based on the group’s average PrEP initiation rate. Participants qualify for US $22 if their group achieves an 80%‐100% rate, US $11 for a 50%‐79% rate, and US $0 for rates below 50%. PrEP initiation is operationally defined as the documented provision of a physician-issued prescription.

The WeChat mini-program automatically records intervention process evaluation indicators, including: (1) whether each participant has read the information messages; (2) the reading time for each message; and (3) each participant’s judgment of whether the information was helpful.

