### Outcomes

The primary outcome indicator of this study is the rate of PrEP initiation, based on formal PrEP prescriptions issued by doctors. The secondary outcome indicators include medication adherence rates after initiating PrEP (based on self-reported adherence and the medication calendar in the mini-program), intention to pay for PrEP (for 3 types of PrEP), PrEP stigma, changes in condom use, and changes in number of sexual partners before and after PrEP use.

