### Ethical Considerations

The study protocol was approved by the Ethics Commission of Peking University Health Science Center (IRB00001052-24167) on December 22, 2024. Prior to study initiation, all participants are fully informed about the study objectives, procedures, potential risks, and their rights, and provide written informed consent. Participants receive a compensation of US $2.8 (approximately CNY 20) for completing each questionnaire at baseline and follow-up assessments. The study does not provide free PrEP medication; participants are required to purchase medications at market prices. To protect participant privacy and confidentiality, several measures have been implemented: data collection uses a customized WeChat mini-program featuring local data storage and optional fingerprint authentication for enhanced privacy; all questionnaires are administered anonymously and linked only via a unique study ID; and sexually transmitted infections test results (HIV, syphilis, hepatitis B, and hepatitis C) are recorded solely as binary (positive or negative) outcomes without any personally identifiable information.

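### The primary endpoint counts a prescription as PrEP initiation, and the group payment in HAPA+GCEI alone depends on the same event, so part of any HAPA+GCEI advantage could be unfilled prescriptions

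*Protocol article*

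**What the plan says.** All references are to the protocol article.

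- **Endpoint.** Under Outcomes: "The primary outcome indicator of this study is the rate of PrEP initiation, based on formal PrEP prescriptions issued by doctors". The abstract describes it as physician-prescribed initiation at 3 months.
- **Incentive.** Under Conditional Economic Incentives: "PrEP initiation is operationally defined as the documented provision of a physician-issued prescription". The same section says: "Group-level economic incentives are stepwise reduced based on the group’s average PrEP initiation rate". The tiers are US $22 for a group rate of 80-100%, US $11 for 50-79% and nothing below 50%, in groups of six.
- **Who is paid, and when they know.** "Participants in the combined intervention arm also receive additional peer GCEIs on top of the HAPA intervention", and "Incentive information is communicated immediately at the start of the intervention".
- **Who buys the drug.** Under Ethical Considerations, "participants are required to purchase medications at market prices". The Introduction puts generic oral PrEP at US $28-42 a month, or about US $5.6 per use when taken on demand.
- **Measures of use.** Adherence after initiation is a secondary outcome, from self-report and the mini-program's medication calendar (Outcomes). The follow-up questionnaire asks about PrEP status, reasons for not starting or for stopping, and where the drug was obtained (Measurements and Follow-Ups).
- **Sample size.** The calculation uses usage rates, 5% against 20%, not prescription rates (Study Population and Participant Recruitment).

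**The concern.** A participant who receives a prescription and never obtains the drug counts in full as having initiated PrEP. That can happen in any arm. Only in HAPA+GCEI, however, does a payment depend on how many group members hold a prescription, and members know this from the start. Any excess of unfilled prescriptions that the payment produces goes straight into the primary comparison of HAPA+GCEI with HAPA and with control.

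The trial sets out to close the gap between intention and behaviour, and it names cost as a main barrier. Where patients pay for the drug, much of that gap can lie between prescription and purchase, a step the primary endpoint does not observe. The adherence outcome does not fill this hole: it is defined only among those who have initiated, so it is not a comparison of all randomised participants. At stake is whether a positive result can be reported as more initiation or uptake, or only as more prescriptions.

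**Working it through.** **1. The plan's own figure.** Inputs: 5% vs 20%, two-sided alpha 0.05, power 90%. With the pooled-variance formula

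n = [1.96·√(2·p̄(1−p̄)) + 1.2816·√(p₁(1−p₁) + p₂(1−p₂))]² / (p₂−p₁)², p̄ = 0.125,

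the result is 101 per group, against 100 stated. Power at 100 per group is 90.0%. The stated figure reproduces.

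**2. Chance of a significant result when true starts are equal.** The documents give no fill rate, so the rates here are assumptions. Analysed n is 126 × 0.85 = 107 per arm. True starts are 20% in both HAPA and HAPA+GCEI.

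Probability = Φ[(d − 1.96·se₀)/se₁], with se₀ = √(p̄(1−p̄)·2/n) and se₁ = √((p₁(1−p₁) + p₂(1−p₂))/n).

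Every HAPA prescription filled; 10 or 15 points of HAPA+GCEI prescription-only:
- 20% vs 30%: se₀ = 0.0592, se₁ = 0.0588, (0.10 − 0.1160)/0.0588 = −0.27, probability **39%**
- 20% vs 35%: se₀ = 0.0610, se₁ = 0.0602, (0.15 − 0.1197)/0.0602 = 0.50, probability **69%**

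Five points of HAPA also prescription-only, so the net excess is 5 or 10 points:
- 25% vs 30%: se₀ = 0.0610, se₁ = 0.0610, (0.05 − 0.1197)/0.0610 = −1.14, probability **13%**
- 25% vs 35%: se₀ = 0.0626, se₁ = 0.0623, (0.10 − 0.1228)/0.0623 = −0.37, probability **36%**

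With all 126 per arm analysed, the first pair becomes 45% and 76%.

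**3. Smallest excess that reaches P<.05 at the actual arm sizes** (chi-square without continuity correction; HAPA 128, HAPA+GCEI 126, control 127).
- Against control at about 5% (6 of 127), with 6 true starts in HAPA+GCEI: 9 extra unfilled prescriptions give 15 of 126 vs 6 of 127, P=.038. Eight give P=.060.
- Against HAPA at about 20% (26 of 128), with 26 true starts in HAPA+GCEI: 14 extra give 40 of 126 vs 26 of 128, P=.038. Thirteen give P=.052.

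**4. How strong the payment's pull is.** In a group of six, 50% means at least 3 prescriptions (US $11) and 80% means at least 5 (US $22). If members act independently, the binomial distribution with n = 6 gives:
- prescription rate 20%: 90% of groups are paid nothing; mean payment US $1.11 per person
- prescription rate 30%: 74% are paid nothing; mean US $2.93
- prescription rate 35%: 65% are paid nothing; mean US $4.13

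**The case against.** The strongest reply concerns the strength of the mechanism. A reader might infer that each prescription triggers cash. It does not: payment follows the group's rate. At the prescription rates assumed in step 2, most groups would earn nothing if members act independently, so it is not obvious that 10 to 15% of the arm would seek a prescription for that money alone. As the tiers are worded, a member without a prescription could even be paid, although the section also mentions each participant's own completion status. This stands, and it makes the pull possibly modest. It does not remove the concern: groups meet in person, know the tiers and are meant to build shared accountability, so independent behaviour cannot be assumed.

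The assumed rates are also open to challenge. Non-filling can occur in every arm, and only the excess in HAPA+GCEI biases the comparison, hence the fall to 13% and 36%. The cost argument cuts both ways: a month of daily PrEP costs more than the top payment, but one on-demand use costs less than either payment.

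A reader might further infer that participants hand in prescriptions to claim the payment. The article does not describe how prescriptions are collected, and that detail may sit in the full protocol.

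Finally, a prescription is a legitimate outcome, the abstract labels it openly, and the follow-up questions would reveal some unfilled prescriptions. That is true, but the article gives those data no role in the conclusion.

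**Conclusion.** The point holds as a limit on interpretation. The endpoint and the payment rest on the same event, the payment exists in one arm only, and nothing in the endpoint confirms that the drug was obtained. Part of a HAPA+GCEI advantage over HAPA or over control could therefore be unfilled prescriptions. HAPA versus control is not affected by the payment.

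The size is conditional. Across the scenarios shown at 107 per arm, with equal true starts of 20%, the chance of a significant HAPA+GCEI vs HAPA result runs from 13% to 69%. At the actual arm sizes and the assumed base rates, 9 extra unfilled prescriptions against control or 14 against HAPA are enough.

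Two stronger readings are not supported. One is that an observed advantage will be an effect of payment for paperwork: no fill rate is given and the group rule weakens the individual motive. The other is that the primary endpoint must be replaced: all 381 participants are already randomised, and the alternative rests partly on self-report.

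**What to change.** Keep the prescription endpoint as primary and leave the incentive scheme unchanged. Before database lock, planned for December 2026:

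1. Name prescription plus confirmed start (drug obtained or first dose taken) as the key secondary endpoint, analysed in all randomised participants. Derive it from the follow-up questionnaire items on PrEP status and source of medication. Use the medication calendar as support only where all arms have it; the Control section describes only push notifications.
2. State that prescriptions are ascertained by the same route in all three arms.
3. Claim increased PrEP initiation or uptake for HAPA+GCEI only if both endpoints agree. Otherwise word the conclusion as increased prescription.

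The cost is one added endpoint definition and one analysis of follow-up items already planned. The downsides are real: confirmed start is partly self-reported, in an arm that knows about the payment; its rate will be lower than the prescription rate; and the HAPA+GCEI claim becomes somewhat harder to make.
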